### Dropout and suspension criteria

Under the protection of the Declaration of Helsinki [26], patients are allowed to withdraw themselves from the clinical research at any time. In addition, if the intervention time is below 3 months, subjects will be considered as not completed the outcome evaluation.

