### Sample size calculation

The PASS software (PASS 11, NCSS, LLC, Kaysville, UT, USA) will be used to estimate the sample size utilizing two independent sample means (*α* = 0.05, *β* = 0.10). We will use the mMRC Scale as the primary efficacy outcome. Based on previous clinical studies on the effect of respiratory symptoms after KQG interventions, the mMRC Scale score in the control group is 0.74 with a standard deviation of 0.55, and the average mMRC Scale score in the treatment group is 1.52 with a standard deviation of 0.54 [25, 40, 41]. The target sample size will be 60 participants in each group based on 80% power, 5% type I error, and two-sided test, anticipating on maximum loss to follow-up of 20%.

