#### Analysis of primary outcome

The primary outcomes will be evaluated at baseline, 12 weeks after the intervention, and follow-up. We will conduct sensitivity analyses for missing data (intention-to-treat analysis) and for adjustment of covariates of physical activity (adjusted intention-to-treat analysis). The primary endpoint is the mean change in mMRC Scales from baseline to the follow-up day. Baseline covariates included are sex, age category, history of cardiopulmonary disease, and body weight category. The whole outcomes scale will be measured at baseline. When normally distributed, the data will be analyzed with unpaired *t*-test for comparison between two groups, while for multiple comparisons one-way ANOVA and repeated measures (RM) ANOVA will be used. A sensitivity analysis using multiple imputation techniques (imputation using chained equations) will be included to assess the effect of missing data on the primary outcome. Besides, we will compare participants randomly allocated to BT group or KQG group, who received an allocated treatment that was deemed to be of high fidelity. The percentage of missing data is 20% and 5 imputed datasets will be used for analysis, which is the minimum recommended number. Prior to any analysis, any missing data pattern will be investigated and the reasons for missing data will be obtained and patterns will be investigated to judge the plausibility of missingness assumptions.

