#### Analysis of secondary outcome

Analysis of secondary outcome will be undertaken referring to analysis of primary outcome. We will test for between arm differences for each endpoint specified. Chi-square test or Fisher’s exact test will be adopted to analyze the adverse events (AEs).

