### Safety evaluation

Safety evaluations will be conducted at screening, throughout the trial, and at follow-up 12 weeks after the last TCMRE, although TCMRE programs are low risk. Any adverse events (AEs) will be collated from CRFs and follow-up questionnaires. Even though BT and KQG are at low risk. AEs will be collated from CRFs and follow-up questionnaires. Researchers will then analyze whether AEs are directly related to the rehabilitation program. When sports injuries occur or condition suddenly deteriorates during the trial with serious complications or severe adverse effects such as breathing difficulties, severe anxiety, severe depression, the trial will be terminated immediately and prompt medical treatment will be administered according to the condition of the subject. Researchers will then analyze whether they are directly related to the rehabilitation program.

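### Stopping exercise before 3 months counts as an uncompleted outcome evaluation, even when worsening caused the stop, so poor outcomes can drop out of the primary comparison

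*Protocol article*

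**What the plan says.** **Dropout and suspension criteria.** After the right to withdraw, the section adds that "if the intervention time is below 3 months, subjects will be considered as not completed the outcome evaluation". The reason for stopping plays no part.

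**Safety evaluation.** For a sports injury, or a sudden deterioration with serious complications or "severe adverse effects such as breathing difficulties, severe anxiety, severe depression", the section says that "the trial will be terminated immediately and prompt medical treatment will be administered according to the condition of the subject". Since it goes on to the treatment of one subject, this is evidently meant to end that person's participation, not the study. A safety contact is planned 12 weeks after the last exercise session.

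**Analysis of primary outcome.** The endpoint is the mean change in mMRC from baseline to follow-up, compared by unpaired t-test or ANOVA. Intention-to-treat enters as follows: "We will conduct sensitivity analyses for missing data (intention-to-treat analysis"). Multiple imputation is also a sensitivity analysis. The section promises that "the reasons for missing data will be obtained and patterns will be investigated to judge the plausibility of missingness assumptions", and adds a comparison of participants "who received an allocated treatment that was deemed to be of high fidelity".

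**Analysis of secondary outcome.** A chi-square or Fisher's exact test "will be adopted to analyze the adverse events (AEs").

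**Sample size calculation.** The plan is "anticipating on maximum loss to follow-up of 20" per cent.

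Nowhere does the article say that someone who stops exercising early is still assessed on the scales.

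**The concern.** Stopping the exercise and missing an assessment are different events. The dropout rule merges them, so whether a participant has a completed outcome depends on how long he or she exercised.

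The safety rule then supplies a reason for stopping that is tied to the outcome. mMRC grades breathlessness, Borg and the respiratory symptom scale also record it, and PHQ-9 measures depression. A participant stopped for worsening breathlessness is thus one with a poor mMRC value, and is the one counted as not evaluated. (Sports injury and anxiety, also named as triggers, are not measured by these scales.)

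If values are missing because they are poor, the observed mean of that arm is too favourable. The arms differ in physical demand: KQG has stances, kicks and heel stamps, while the control arm does seated and paced breathing. The number of stops and the reasons for them could therefore differ by arm. No later analysis plan can recover values that were never collected.

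**Working it through.** **Inputs from the protocol.** 30 per arm (Fig. 1 caption). SD 0.55 for control (BT) and 0.54 for treatment (KQG), with means 0.74 and 1.52 and hence a difference of 0.78 (Sample size calculation). Loss ceiling 20%, so 0.20 × 30 = 6 per arm. The 0.78 is used only as a yardstick: as printed, the treatment mean is the higher and so the worse one on mMRC, but the shifts below do not depend on its direction.

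**Assumptions not in the protocol.** How many stop in each arm; that those lost are the worst scorers of their arm; that the score SDs apply to the change; and normal scores, although mMRC is a 0–4 grade.

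**Step 1: shift in one arm.** Draw 30 normal scores, remove the worst k, and average the rest (200,000 draws). Shift in grades = shift in SD units × SD.

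| Lost, k | SD units | BT (× 0.55) | KQG (× 0.54) |
|---|---|---|---|
| 1 | 0.070 | 0.039 | 0.038 |
| 3 | 0.186 | 0.102 | 0.100 |
| 6 | 0.338 | 0.186 | 0.183 |

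**Step 2: error in the arm difference** = shift in one arm − shift in the other.

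- Equal counts, worst scorers in both arms (1 vs 1, 6 vs 6): about 0.00.
- 0 vs 1: at most 0.039; 0.039 / 0.78 = 5%.
- 3 vs 6: 0.080 if KQG loses 6, 0.086 if BT does; 0.086 / 0.78 = 11%.
- 0 vs 6: 0.183 to 0.186; 0.186 / 0.78 = 24%.

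If a single lost participant is instead d grades worse than the completers, the shift is k × d / 30. With an assumed d of 2.28 (no source in the protocol) this is 1 × 2.28 / 30 = 0.076. If the 60 per group printed in the sample size section is meant, losing 1 gives 0.02 and losing 12 (20%) gives 0.19.

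**Step 3: equal counts with different reasons.** Suppose there is no true effect and both arms lose a fraction q, at random in one arm and from the worst scorers in the other. Then spurious difference = SD × φ(c) / (1 − q), where c cuts off the worst fraction q and SD = 0.545. For q = 0.20: 0.545 × 0.280 / 0.80 = 0.19. At 5%, 10% and 20% loss the difference is 0.06, 0.11 and 0.19 grade, and the two-sided type I error is about 7%, 12% and 28% instead of 5%. If only half of that arm's losses are worst scorers, it is about 6%, 7% and 11%. Equal dropout counts are therefore no guarantee.

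**Step 4: does imputation repair it?** Simulation (3,000 runs, 5 imputations within arm, worst k lost, predictor correlated r with the outcome). Bias left, in grades:

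| Lost | r = 0 | r = 0.3 | r = 0.5 | r = 0.7 |
|---|---|---|---|---|
| 0 vs 1 | 0.038 | 0.035 | 0.029 | 0.021 |
| 3 vs 6 | 0.082 | 0.078 | 0.070 | 0.057 |
| 0 vs 6 | 0.183 | 0.171 | 0.153 | 0.115 |

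For 0 vs 6, imputation removes (0.183 − 0.153) / 0.183 = 16% at r = 0.5 and (0.183 − 0.115) / 0.183 = 37% at r = 0.7.

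**Step 5: does the safety contact close the gap?** If it is counted from a participant's own last session, someone who stops at week 4 is seen at week 4 + 12 = 16, not at the scale assessments at weeks 12 and 24. If it is counted from the scheduled end of treatment, it falls at week 24, but the section describes a collection of adverse events, not of the scales.

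**The case against.** The strongest reply is that the decisive step is not printed. The dropout rule labels early stoppers; it does not say that they are no longer assessed, that their data are deleted, or that they leave the analysis. The separate high-fidelity comparison would be nearly redundant if the main set were already completers, which speaks for a wider main set. The bracketed mention of intention-to-treat could name the framework of the sensitivity analyses rather than demote it. This is also a condensed article, and analysis-set definitions commonly sit elsewhere. All of this stands as a limit on certainty: a completer-only primary comparison is an inference. It does not remove the rule, which is a positive statement. Staff who follow it have no reason to assess an early stopper.

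Second, missing data are not ignored. Reasons and patterns will be examined, imputation is planned, and adverse events are compared by arm. These steps can reveal differential stopping, but the first and last recover no values, and imputation recovers them only in part (step 4).

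Third, the 24% is an extreme: six lost against none, all of them worst scorers, with an all-cause loss ceiling standing in for stops due to deterioration. Participants must be stable, major comorbidity is excluded and the exercises are described as low risk, so such stops may be rare. This stands, and it is why the result is given as a range.

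**Conclusion.** The concern holds as a possibility that the plan's own rules create. Completion of the outcome evaluation is tied to 3 months of exercise whatever the reason for stopping, deterioration in the measured symptoms is a reason for stopping, and only sensitivity analyses are described as intention-to-treat. Poor outcomes can therefore be lost from the primary comparison.

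The size is 0 to 0.19 grade, or 0% to 24% of the 0.78 planning difference, on the assumptions listed in the working. With at most one such stop per arm it is about 0.04 grade, or 0.08 under the assumed 2.28-grade excess. The direction depends on which arm loses more poor outcomes, which the protocol does not give. The point should be corrected, with medium confidence that it would matter in practice.

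**What to change.** **Dropout and suspension criteria.** Replace the rule with wording such as: *Participants who stop exercising before 3 months, for any reason, are still assessed on all scales at 12 and 24 weeks from the start of the intervention unless they withdraw consent; the date and reason for stopping are recorded.*

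**Analysis of primary outcome.** Make the analysis of all randomised participants in their assigned arm the primary one, with multiple imputation and the high-fidelity comparison as secondary. Optionally, add a sensitivity analysis that gives a poor value (for example baseline grade + 1, maximum 4) to participants stopped for deterioration who cannot be assessed.

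**Safety evaluation.** Say that the participant's exercise is stopped, rather than the trial. The clinical triggers stay as they are.

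**Cost.** Wording in three sections, and scales at assessment times already planned. Some effort is needed to follow participants who have stopped. The poor-value rule is too pessimistic for an episode that resolves with treatment, so it should remain a sensitivity analysis.

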### Interventions

In this study, a total of 60 recruited participants will be randomized into the BT group or the KQG group. Both exercises last 15 min per time and each program will be performed twice a day at 10 am and 4 pm [27]. Thus, a total of 30 min will be needed every day [28]. A 3-week treatment comprised one course. The intervention will last for 3 months in both our groups and then both will be followed up for a further 3 months.

The exercise of both groups will be demonstrated and monitored by the therapists on the first day until the patient is able to perform the exercises proficiently. Text instruction and video demonstration of the exercises will be provided to patients for subsequent practice. After patients are familiar with the basic movements, they can increase the intensity and focus on the breathing under the guidance of the therapists. Therapists performing TCMRE will be required to have a minimum of 10 years’ clinical experience in Qigong therapy, and they must have undergone meticulous clinical trial training before conducting trials until passing an exam to perform the intervention. In addition, participants in both groups will be allowed to exercise normally under intervention conditions.

The exercise of both groups will be demonstrated and monitored by the therapists on the first day until the patient is able to perform the exercises proficiently. Paper and video versions of the exercises will be provided to patients for subsequent practice. After patients are familiar with the basic exercise, they can increase the intensity and focus on the breathing under the guidance of the therapist. Therapists performing TCMRE will be required to have a minimum of 10 years clinical experience in Qigong therapy. And they must have undergone meticulous clinical trial training before conducting trials until passing an exam to perform the intervention. In addition, participants in both groups will be allowed to exercise normally under intervention conditions.

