### Inclusion criteria

Patients with the following criteria will be recruited:

(1) discharged patients with COVID-19; (2) are male or female between the ages of 20 and 80; (3) have post-COVID-19 symptoms include but not limited to breath difficulties, fatigue, sleep difficulties, anxiety, or depression; (4) have a stable condition and remain conscious and cooperative during trial; (5) willing to join the trial and signed the informed consent form; (6) promise not to participate in other forms of exercise.

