### Exclusion criteria

Any involvement in the following condition will be removed: (1) patients with complications of underlying noncommunicable diseases such as chronic obstructive pulmonary disease, coronary heart disease, dementia, chronic kidney disease, immunosuppression, and cancer; (2) patients with mental illness; (3) patients with cognitive dysfunction until unable to understand the whole trial process; (4) patients with severe bone or joint diseases that affect movement (e.g., spinal arthritis, severe osteoporosis, and periarthritis); (5) patients with pregnancy or lactating; (6) cigarettes smokers; (7) patients who participate in other form of exercise programs during trial.

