
### Adherence

This will be home respiratory training program with compliance assessed every week by telephone calls and review of the everyday charts filled-in by participants. The participants will be informed to perform breathing techniques or KQG exercises every day at 10 am and 4 pm. Remote monitoring devices will be offered to every ward so that remote monitoring of the training of the subject can be achieved. The participants will be required to sign in a recorded diary after each exercise.

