### Blinding

We will use a concealed randomization where neither participant nor researcher was aware of the randomization until after the baseline interview. None of the participants or clinicians will be blinded to treatment allocation after randomization, due to the specific exercise intervention. However, they will be blinded to the outcome assessment. Evaluation of the outcomes will be accomplished by independent evaluators (IEs), including the outcome assessors, the data managers, and the statisticians. IEs will be blinded until the clinical database is locked.

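### The protocol gives inconsistent scopes for permitted non-study exercise, and exclusion (7), applied as written, would remove participants after randomisation for conduct during the trial.

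*Protocol article*

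**What the plan says.** Three sections of the Protocol article deal with exercise outside the allocated programme.

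- **Inclusion criteria, item (6):** patients must "promise not to participate in other forms of exercise".
- **Exclusion criteria, item (7):** the list names "patients who participate in other form of exercise programs during trial". It is introduced by the words "Any involvement in the following condition will be removed".
- **Interventions:** "participants in both groups will be allowed to exercise normally under intervention conditions". The sentence appears twice because the paragraph is printed twice in nearly the same words. The repetition is not independent confirmation.

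Four other sections bear on the consequence.

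- **Dropout and suspension criteria** allows voluntary withdrawal and adds that "if the intervention time is below 3 months, subjects will be considered as not completed the outcome evaluation". It does not mention non-study exercise.
- **Blinding:** "None of the participants or clinicians will be blinded to treatment allocation after randomization". Assessors, data managers and statisticians stay blinded until database lock.
- **Adherence** provides for "compliance assessed every week by telephone calls and review of the everyday charts filled-in by participants".
- **Analysis of primary outcome** names intention-to-treat in the sentence on sensitivity analyses. It also plans an adjustment for physical activity, multiple imputation, and a comparison of participants whose treatment was of high fidelity.

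**The concern.** There are two linked problems.

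The first is scope. Both interventions are home exercise, and the outcomes are dyspnoea, fatigue, mood, sleep and respiratory symptoms. Other exercise is therefore an obvious co-intervention, and the rule on it should be clear. One section bars other forms of exercise, one bars other exercise programmes, and one permits normal exercise. Staff and participants could reasonably apply different rules.

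The second is timing. Exclusion criteria are meant to be settled before randomisation. The first six items are worded as states that can be checked at entry, whereas item (7) is worded as conduct while the trial runs. Someone who starts another programme after allocation meets it only then, and the only stated consequence is removal. Removing randomised participants for post-randomisation behaviour can undo the comparability that randomisation gives, particularly when participants and clinicians know the allocation.

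**Working it through.** The point rests mainly on setting the sections side by side.

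**Step 1: scope.**

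| Section | Wording covers | Direction |
|---|---|---|
| Inclusion (6) | any other form of exercise | barred |
| Exclusion (7) | other exercise programmes, during the trial | barred, with removal |
| Interventions | normal exercise, under intervention conditions | allowed |

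Inclusion (6) is the broadest ban. Exclusion (7) may be narrower, because a programme suggests something structured. The Interventions sentence has at least three readings: non-study exercise is allowed, usual daily activity is allowed, or the allocated exercise is to be done as usual. The first contradicts both bans. The second fits exclusion (7) but sits uneasily with inclusion (6). The third fits both. The article does not choose between them.

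**Step 2: when exclusion (7) can be met.** Interventions gives 3 months of intervention and a further 3 months of follow-up. The post-randomisation period in which the conduct could occur is therefore 3 + 3 = 6 months.

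**Step 3: what follows if it is applied as written.** The heading of the exclusion list says removal. If that happens within the intervention period, the participant's intervention time is below 3 months, and the dropout section then classes that person as not having completed the outcome evaluation. It does not say that the person leaves the analysis. Whether intention-to-treat is compromised depends on what comes next:

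- If follow-up continues and the participant is analysed as randomised, there is no conflict.
- If follow-up stops, the outcome is missing, and the planned sensitivity analysis and imputation have to cover it.
- If the participant is dropped from the analysis, the comparison is no longer of all those randomised.

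**Step 4: scale.** The Fig. 1 legend gives 30 patients per group, so each removal is 1/30 = 3.3% of an arm. Sample size calculation gives 60 per group; on that figure it is 1/60 = 1.7%. The disagreement between those two group sizes is a separate matter. These percentages show only what one participant weighs. They do not predict how many would be removed.

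**The case against.** The strongest reply is that a coherent reading exists: no other exercise programmes, but ordinary activity allowed. The Interventions sentence closes a paragraph about the allocated exercise, is qualified by its reference to intervention conditions, and does not mention other programmes. The control technique is itself practised during effortful activity such as climbing stairs, so ordinary activity can hardly be banned. The planned adjustment for physical activity also expects activity to vary. This stands as far as it goes: the wording is an inconsistency of scope that a narrow reading could resolve. The article does not state that reading, and it leaves the broader ban in inclusion (6) unexplained.

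The second reply is that removal most naturally means exclusion at entry. The heading covers all seven items, Participant recruitment places the check of criteria at screening, and the dropout section has no rule on other exercise. That may well be the intention. It does not fit the words of item (7), which refer to the trial period.

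A reader might go further and infer that unblinded staff would decide who is removed. The protocol does not say so. It states that clinicians are unblinded but names nobody to judge a breach; monitors verify eligibility criteria, and a steering committee oversees the trial. A reader might also infer a direct conflict with intention-to-treat. That too is unsupported, because the dropout section speaks of non-completion and not of exclusion from analysis.

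It is also fair to say that detailed deviation handling belongs in a full protocol. The point here concerns rules that the article does state.

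**Conclusion.** The point holds in a limited form. The three statements on non-study exercise do not share one scope, and exclusion (7), if applied as written, would remove participants after randomisation in a trial where participants and clinicians are unblinded. Any harm to the intention-to-treat comparison is conditional: removals would have to happen, and follow-up or analysis would then have to stop for those removed.

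The consequence is modest. The protocol gives no basis for saying that removals would occur, how many there would be, or that they would differ between arms, so no size of bias and no loss of power is claimed. The correction is still worth making, because it changes a stated rule at almost no cost.

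**What to change.** 1. State one rule in Inclusion criteria, Exclusion criteria and Interventions: no structured exercise programme beyond the allocated one, with usual daily activity allowed.
2. Limit exclusion (7) to participation in another exercise programme at screening.
3. Record any later breach as a protocol deviation on the daily chart or in the weekly call already planned under Adherence.
4. State that a breach does not end participation: everyone randomised stays in follow-up and in the intention-to-treat analysis.

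The cost is a wording change in three sections, with no new visit or instrument. The downside is that participants who exercise elsewhere remain in the comparison, which may dilute the contrast between arms. The high-fidelity comparison already planned could show how much that matters, if outside exercise is counted in the definition of fidelity.
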